### Endpoints

The trial primary endpoint will be the difference in AAA growth between the intervention and control groups over 24 months. AAA growth will be assessed by 1) maximum infra-renal aortic volume on CTA, 2) maximum orthogonal diameter on CTA, and 3) maximum diameter on ultrasound. Infra-renal aortic volume can be measured in a reproducible way and changes in it appear to provide a more sensitive means to assess AAA growth [49]. It is expected that a number of participants may not receive a CTA at 24 months due to drop-out, for example due to requirement for AAA surgery. We therefore have also included ultrasound measured AAA growth as a primary endpoint since ultrasound assessments will be performed every 6 months.

CTA will be obtained at entry, 12 and 24 months depending on local ethics guidelines (CTA at entry and 24 months only for Stanford and Leiden study centres). Assessment of infra-renal aortic volume will be performed according to a previously established protocol at the main study centre (mean inter-observer coefficient of variation = 2.7 %) [49]. The total volume of the infra-renal aorta, including the aortic wall and lumen, will be estimated using a semi-automated program that we have previously established to be reproducible [49]. In short, axial regions of interest are drawn around the aorta from the slice inferior to the origin of the lowest renal artery to the slice superior to the bifurcation of the aorta. The areas of these regions of interest are summated using CT analysis software to yield an overall volume. The maximum orthogonal AAA diameter on CTA is a measurement of infra-renal aortic diameter perpendicular to the lumen, devised to avoid over-estimation of tortuous AAAs. We have previously reported a reproducible protocol to measure orthogonal aortic diameter (mean inter-observer coefficient of variation = 3.5 %) [50]. Initially, seeds are placed in the centre of the infra-renal aorta from the renal arteries to the aortic bifurcation. Curved multi-planar reconstruction is then used to reconstruct the aorta perpendicular to its axis. The reconstructed aorta is subsequently scouted to find the region of maximum diameter, taking many measurements. The largest diameter is taken to be the maximum orthogonal diameter.

Ultrasound measurements will be undertaken at entry, 6, 12, 18 and 24 months. Maximum anteroposterior and transverse infra-renal aortic diameter will be measured by experienced sonographers using a 3.75-MHz transducer and ultrasound machines present in vascular laboratories of each centre. Diameters will be measured in the plane of the aorta with callipers placed on the outer part of the aortic wall. The largest external anterior-posterior and transverse AAA diameters will be recorded. The location at which the maximum diameter is measured will always be within the infra-renal aorta but will be selected based on the maximum diameter not particular location within this artery segment. The intra-observer reproducibility of ultrasound measurements has been assessed at major participating centres and shown to be good (coefficient of repeatability ≤1.6 mm for four reporting centres) [18, 31]. Central analysis of both CTA and ultrasound images will be performed at the study centre.

Secondary endpoints include change in resting brachial blood pressure, AAA biomarker profile, and health-related quality of life. Resting brachial blood pressure will be measured at entry, 3, 6, 12, 18 and 24 months. Three blood pressure measurements will be recorded at 3-minute intervals, with the average blood pressure used as the representative value. Blood will be taken at entry, 6, 12, 18 and 24 months to assess changes in circulating AAA biomarkers. The AAA biomarker panel will include OPN, OPG, D-dimer, TGF-β1 and MMP-9, and will be measured centrally. These circulating proteins have been selected based on extensive evidence suggesting that they have a central role in AAA pathology [39, 51]. Health-related quality of life will be assessed by the Short Form-36 (SF-36) questionnaire collected at entry, 12 and 24 months. The SF-36 has previously been validated for use in elderly patients with vascular disease [52, 53].

Additional outcome data recorded will include requirement for AAA repair surgery as determined by the treating vascular surgeon, AAA rupture, all-cause mortality, acute cardiovascular events, withdrawal from study medication, drug safety and changes in background medication. Medication compliance will be assessed by hand-counting of pills during scheduled visits.

### Sample size and power calculations

At present there is insufficient preliminary data demonstrating an accurate effect size of AT1 blockers on AAA growth. In line with other AAA drug trials, we estimated our sample size based on a clinically relevant reduction of 30 % in annual AAA growth [18]. Given local AAA growth rates (mean = 1.20 mm/y, standard deviation = 1.16) applicable to the study population, we calculated an effect size d = 0.36 [54]. Accordingly, based on t-test analysis, this study requires 126 participants per group (252 in total, power = 80 %, α = 0.05) to detect the hypothesised reductions in AAA growth. Taking into account a 24-month drop-out rate of approximately 20 %, we plan to recruit 300 patients.

### Study organization

The TEDY trial has been developed through an international collaboration of experts in AAA biology, clinical management of AAA, aortic imaging and drug trials. TEDY is a multi-centre study conducted from major vascular centres in Australia, The Netherlands and the USA. The study steering committee comprises senior vascular investigators from the centres involved and experts in drug trials and data analysis (Appendix). This will be the main policy and decision-making committee for the study and will meet by teleconference. Currently, there are nine study centres in total, seven in Australia, one in Leiden, Netherlands, and one in Stanford, California, USA. The Stanford study centre is sponsored by Medtronic Inc. (Santa Rosa, CA) and will utilise independent randomisation, medication concealment and imaging analysis. The core imaging and biomarker laboratories are located at the Vascular Biology Unit, Queensland Research Centre for Peripheral Vascular Disease, James Cook University, Townsville Australia, and the Veteran’s Administration Palo Alto Health Care System, USA. The web-based randomisation database will be managed by the Monash Clinical Trials Centre, Melbourne Australia, with an independent randomisation centre at Stanford University. The Baker IDI Heart and Diabetes Institute will coordinate medication concealment and packaging for Australian centres. The Leiden study centre will coordinate medication concealment locally for convenience. An independent DSMB will review all adverse events and conduct an interim analysis.

### Data handling

Trial documentation including design, eligibility criteria, protocols and case report forms (CRF) will be shared electronically with participating study centres. The online clinical trial portal will house the central web-based randomisation system (https://ccre.med.monash.edu.au/TedyRand/). Data recorded on printed CRFs will be faxed or scanned to the trial coordinating centre where it will be entered centrally and examined for data quality. All participating centres have received local ethics approval and the study is being conducted in accordance with the Declaration of Helsinki. The TEDY trial is registered at www.anzctr.org.au: ACTRN12611000931976. The Stanford arm of the trial is registered at www.clinicaltrials.gov ID: NCT01683084.

### Safety

Previous large randomised control trials have shown telmisartan to have a good safety record [55, 56]. The TRANSCEND trial demonstrated negligible side effects for telmisartan (80 mg od daily) in approximately 6,000 individuals with cardiovascular disease [55]. These findings suggest that telmisartan (40 mg od daily) should be well tolerated by the majority of patients eligible for the TEDY trial. Participant safety will be assessed on all visits and phone calls. Detailed safety assessment will occur at 3, 12 and 24 months and will involve a targeted medical history, physical examination of heart rate and brachial blood pressure, laboratory parameters including serum chemistry (liver function tests, glucose, creatinine, sodium, potassium, chloride) and haematology (haemoglobin, differential white blood cell count and platelet count), and adverse event reporting via report forms provided to study centres. Participant safety will also be assessed by phone calls occurring at 2 weeks, 9 months, 15 months and 21 months. Adverse events may comprise shortness of breath, wheeze, rash, dizziness and fatigue. Possible side effects of the medication include back pain, diarrhoea, respiratory tract infection and sinus inflammation. In line with other medication trials, serious adverse events (SAEs) will be defined as death, requirement for in-patient hospital treatment and persistent or significant disability.

The DSMB will consist of an independent epidemiologist, vascular surgeon and statistician; and will meet to assess all adverse events. In particular, the DSMB will concentrate on AAA-related events such as sudden death due to AAA rupture, as well as adverse events related to study medication. Expected AAA rupture rates for small AAAs are approximately 1 to 2 % per year based on published data [9, 10]. Rupture rates greater than this will be considered to be a cause for concern. In this instance consideration will be given to assessment of all other outcome data from the study. AAA growth will be compared between placebo and telmisartan groups using this data. The final decision to stop the study will take into account AAA ruptures, AAA growth data and any other serious complications. Following their assessment, the DSMB would report their recommendation to the steering committee. One formal interim analysis will be undertaken when 60 % of participants have been followed-up for 24 months. Based on all available data at the time of the interim analysis, the difference in growth at 24 months of follow-up will be estimated and tested.

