**Inclusion criteria**
• Written informed consent
• Infra-renal AAA with maximum orthogonal diameter of ≥35 mm and ≤49 mm on CTA or ultrasound
• No current indication for AAA repair, or expectation that this will be revised in 12 months
• Likely to comply with treatment over 24 months, including seven visits to study centre

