### Statistical analysis

The principal analysis of primary and secondary endpoints will be based on intention to treat at the time of randomisation. All patients who meet the eligibility criteria, provide written informed consent and are enrolled in the study will be included in the primary analysis, regardless of adherence to treatment medication. The efficiency of randomisation will be assessed by comparing the distribution of recognized determinants of AAA progression and also background medication use prior to the study between the treatment and control groups.

The primary efficacy parameter is the between treatment groups difference in mean growth in AAA over 2 years as estimated by the maximum AAA volume on CTA, maximum orthogonal diameter on CTA, and maximum diameter on ultrasound. If there were to be no drop-outs, the observed mean progression over 2 years would be compared and tested using a two-sample t-test. However, it is expected that a non-negligible proportion of patients will drop out before 2 years due to aneurysm repair. Aneurysm growth will therefore be analysed by a linear mixed model, specifying zero difference between treatment groups at baseline. The model will have up to 11 repeated dependent measurements: three CTA volume measurements, three CTA diameter measurements, and five ultrasound measurements.

The fixed part of the model will contain the following covariates: Time for CTA measurements as a categorical, time for ultrasound measurements as a categorical, treatment, interaction between treatment and CTA time, and interaction between treatment and ultrasound time. The covariance part of the model will constitute a linear covariance matrix containing the following parameters: Variance of CTA measurements, variance of ultrasound measurements and covariance parameters. Without reference to the fixed part of the model, the goodness of fit of the assumed covariance model will be investigated. If necessary, the model will be extended with additional terms. The analysis will be performed using the PROC MIXED procedure on SAS (Cary, North Carolina), which is capable of fitting arbitrary linear covariance matrices. The main null hypothesis that will be tested is based on the treatment effect as estimated by this model at 24 months on CTA and ultrasound measurements.

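### The SAE definition is a closed list of three criteria with no limb for life-threatening or otherwise medically important events

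*Protocol article*

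**What the plan says.** The Safety section fixes what is serious in one sentence: "serious adverse events (SAEs) will be defined as death, requirement for in-patient hospital treatment and persistent or significant disability". Just before it, adverse events in general are described by example: "Adverse events may comprise shortness of breath, wheeze, rash, dizziness and fatigue". The same section schedules detailed safety assessments at 3, 12 and 24 months, with liver function, creatinine and electrolytes among the laboratory tests, and provides report forms to sites. It also says that the DSMB "will meet to assess all adverse events", giving particular attention to AAA-related events and to those related to study medication.

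AAA repair appears elsewhere. The Endpoints section states: "Additional outcome data recorded will include requirement for AAA repair surgery as determined by the treating vascular surgeon". The Statistical analysis section adds that "it is expected that a non-negligible proportion of patients will drop out before 2 years due to aneurysm repair". The article does not say whether an admission for repair is also an SAE.

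**The concern.** A definition of seriousness should pick out grave events whatever the care setting. Here, apart from death and lasting disability, the only route to seriousness is in-patient treatment. Two participants with equally dangerous events could therefore be classified differently because one was admitted and the other was treated in an emergency department and sent home.

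What is at stake is the SAE label and the SAE count. A grave event without the label sits among common mild complaints such as dizziness and fatigue, and anyone reading only the SAE table would not see it. This matters somewhat more because the article itself treats kidney function and electrolytes as relevant to telmisartan. Both appear among the contraindications in Table 1 and both are monitored by scheduled bloods, yet an abnormal result can be dangerous without leading to admission.

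**Working it through.** No figure in the article bears on this point, so the check is textual.

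**1. Is the list open or closed?** The wording of "serious adverse events (SAEs) will be defined as death, requirement for in-patient hospital treatment and persistent or significant disability" sets a definition and contains no term that marks examples. The neighbouring sentence "Adverse events may comprise shortness of breath, wheeze, rash, dizziness and fatigue" uses open wording, and so does the next one on possible side effects. The authors therefore signalled examples where they meant examples. The list of SAE criteria reads as closed.

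**2. Does any other text widen it?** The Endpoints, Study organization, Safety and Statistical analysis sections and Table 2 were read for this. None adds a criterion of seriousness. The Safety section says that a decision to stop would also take other serious complications into account, but it does not define that term or tie it to the SAE definition.

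**3. Apply the definition to a test case.** Take a dangerous potassium or creatinine value found at a scheduled safety visit, corrected without admission, with full recovery.
- Death: no.
- In-patient treatment: no.
- Persistent or significant disability: no.
- Result: not an SAE. Provided that the site reports the finding as an adverse event, it is recorded as a non-serious one.

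The same holds for an acute episode of wheeze or breathlessness that is life-threatening at the time and treated without admission.

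**4. How wide is the gap?** An event falls into it only if it meets four conditions together: it is life-threatening or otherwise medically important, it is survived, it is treated without admission, and it leaves no lasting disability. The article gives no adverse event or SAE rate, so the number of such events cannot be estimated.

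**5. Are these events lost to oversight?** No. Table 2 schedules adverse event checks at every contact after randomisation, and the DSMB "will meet to assess all adverse events". The gap concerns classification and counting, not detection.

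**6. AAA repair.** Three statements stand side by side.
- Eligibility (Table 1) requires "No current indication for AAA repair, or expectation that this will be revised in 12 months", so a repair is not planned at entry and arises after enrolment.
- Repair is expected in some participants (Statistical analysis) and recorded as an outcome (Endpoints), where it is listed apart from drug safety.
- The in-patient criterion carries no statement either way on admissions for repair.

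An SAE must first be an adverse event, and the article does not say that an elective repair is one. The classification is therefore unstated. The number of repairs is not given either. The Sample size section says "Taking into account a 24-month drop-out rate of approximately 20" per cent, which for 300 participants is 0.20 × 300 = 60 drop-outs from all causes. The share due to repair is not reported, so 60 cannot be read as a count of repairs.

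**The case against.** The strongest reply is that this is a journal article and the sentence is a summary. The full protocol and the report forms may carry a wider definition, and operational details are properly left to them. That stands for two matters: an exemption for elective admissions, and a clause on prolonged stay (which in-patient treatment arguably covers already). Their absence is no finding. It does not stand for the definition itself. The article is not silent here but states a rule, and the rule as stated misclassifies. If the full protocol is wider, the article reports it wrongly.

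A second reply is that the DSMB sees every adverse event and that ruptures, deaths and acute cardiovascular events are recorded separately. This is correct and limits the consequence to labelling and tabulation.

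Three stronger readings are tempting, and the documents do not support them.
- A reader might infer that every planned admission for repair is an SAE. No section says so, and repair is handled as a separate outcome.
- A reader might infer that the between-arm SAE comparison is biased towards showing no drug harm. That would require repairs to be counted as SAEs and telmisartan to reduce them. With no effect on repair they would only add noise, and with an increase the direction would reverse.
- A reader might infer that the DSMB would miss reactions characteristic of telmisartan. The DSMB reviews all adverse events. Breathlessness, wheeze and rash are given as general examples of adverse events and are not among the side effects that the article attributes to the drug.

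The article also says that its definition follows other medication trials. It cites none there, so this point does not rest on any outside benchmark.

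**Conclusion.** The point holds in a limited form. The stated definition of seriousness has no limb for life-threatening or otherwise medically important events. As written, it excludes such an event from the SAE count when the participant survives, is not admitted and has no lasting disability. The consequence is misclassification in a narrow class of events whose frequency the documents do not allow anyone to estimate. Safety oversight by the DSMB is not shown to be impaired.

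This conclusion assumes that the sentence is applied literally and that the full protocol uses the same definition. If the full protocol is wider, only the article needs correcting.

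The status of admissions for AAA repair is a secondary clarification. No claim is made about how many there will be or about the direction of any bias.

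**What to change.** Add two limbs to the SAE definition in the protocol and on the report form: events that are life-threatening, and other important medical events in the investigator's judgement. If the full protocol already contains them, correct the article's sentence to match.

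As a secondary clarification, state whether an uncomplicated elective admission for AAA repair is counted as an SAE or recorded only as an outcome, and tabulate repair separately in either case, so that all nine centres classify it alike.

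The cost is a change of wording in the protocol and the report form, and a few more SAE forms from sites. The sample size, the visit schedule and the efficacy analysis are not affected.

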### Statistical analysis

The principal analysis of primary and secondary endpoints will be based on intention to treat at the time of randomisation. All patients who meet the eligibility criteria, provide written informed consent and are enrolled in the study will be included in the primary analysis, regardless of adherence to treatment medication. The efficiency of randomisation will be assessed by comparing the distribution of recognized determinants of AAA progression and also background medication use prior to the study between the treatment and control groups.

The primary efficacy parameter is the between treatment groups difference in mean growth in AAA over 2 years as estimated by the maximum AAA volume on CTA, maximum orthogonal diameter on CTA, and maximum diameter on ultrasound. If there were to be no drop-outs, the observed mean progression over 2 years would be compared and tested using a two-sample t-test. However, it is expected that a non-negligible proportion of patients will drop out before 2 years due to aneurysm repair. Aneurysm growth will therefore be analysed by a linear mixed model, specifying zero difference between treatment groups at baseline. The model will have up to 11 repeated dependent measurements: three CTA volume measurements, three CTA diameter measurements, and five ultrasound measurements.

The fixed part of the model will contain the following covariates: Time for CTA measurements as a categorical, time for ultrasound measurements as a categorical, treatment, interaction between treatment and CTA time, and interaction between treatment and ultrasound time. The covariance part of the model will constitute a linear covariance matrix containing the following parameters: Variance of CTA measurements, variance of ultrasound measurements and covariance parameters. Without reference to the fixed part of the model, the goodness of fit of the assumed covariance model will be investigated. If necessary, the model will be extended with additional terms. The analysis will be performed using the PROC MIXED procedure on SAS (Cary, North Carolina), which is capable of fitting arbitrary linear covariance matrices. The main null hypothesis that will be tested is based on the treatment effect as estimated by this model at 24 months on CTA and ultrasound measurements.

It is possible that participants randomised to telmisartan may have a small reduction in blood pressure. In the event that the control group are more frequently receiving other blood pressure modifying medications at the completion of the trial, post-hoc analyses will be conducted with appropriate adjustment for these confounding factors.

The stopping boundaries are based on the alpha and beta spending function theory and the stopping rule preserves the overall probability of 0.05 of rejecting the null hypothesis in favour of telmisartan while the null hypothesis is true [57]. The stopping rule is flexible in the sense that the actual time of the interim analyses may deviate from the scheduled time and that more interim analyses may be inserted. The stopping rule is designed using SAS PROC SEQDESIGN. We have chosen a gamma cumulative spending function with gamma parameter equal to −5 for alpha and −7 for beta. These choices lead to conservative stopping boundaries, such that the trial will stop for superiority only if the evidence for a favourable telmisartan effect is very strong and the trial will stop for futility only if the interim analysis suggests it very unlikely that a significant telmisartan effect will be found at the end of the trial. At the interim analysis, the trial will stop for superiority if the one-sided *P* value in favour of telmisartan is smaller than 0.0032. The trial will stop for futility if the one-sided *P* value is larger than 0.5.

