**Fig. 1 Fig1:**
[figure not shown]
Design of the Telmisartan in the management of abdominal aortic aneurysm (TEDY) Trial

Eligible participants who have provided written informed consent will return for a randomisation visit, during which they will be allocated to either telmisartan (40 mg od daily) or matching placebo (once daily) for 24 months. Patients will be randomised by a blinded health professional through the secure trial website, coordinated by an independent trial centre. Treatment allocation will be determined by a computer-generated random number sequence that is stratified by study site and initial aortic diameter (35 to 39 mm, 40 to 44 mm, and 45 to 49 mm). Random number sequences will correspond to serial numbers on concealed study packaging. Only the trial drug centre and the Data and Safety Monitoring Board (DSMB) will know the identity of pre-packaged drugs. The Stanford study centre will utilize an independent randomization procedure implemented locally, whereby ID numbers are randomly allocated to the two study groups using randomization software (www.tufts.edu/~gdallal/randomize.htm). The resultant randomization key will be provided to the on-site pharmacy, which dispenses study medication to participants according to the condition assignment prescribed by the key.

Following randomisation, participants will receive their allocated study medication and subsequent instruction on the dosing regimen. Individuals will be contacted by phone 2 weeks after randomisation and asked about adherence to study treatment and known medication side effects. Phone consultations will be repeated at 9, 15 and 21 months. Follow-up visits will occur at 3, 6, 12, 18 and 24 months, during which the occurrence of trial endpoints and adverse events will be appraised. Participants will receive ongoing health questionnaires, clinical examination, blood tests and imaging according to Table 2. All participants, including those in whom allocated medication is discontinued, will be invited to follow up for the duration of the study in the absence of AAA repair. Final follow-up will occur at 24 months after randomisation, at which point the participant will discontinue the prescribed medication.

**Table 2 Tab2:** Visit schedule

	Study time points (months)										
	0	0	½	3	6	9	12	15	18	21	24
Assessment	Visit 1	Visit 2	Phone Call	Visit 3	Visit 4	Phone Call	Visit 5	Phone Call	Visit 6	Phone Call	Visit 7
Consent	x										
Enrolment/randomisation		x									

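### Allocation is stratified by study site, but the primary mixed model's stated fixed effects leave site out, at some cost in precision

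*Protocol article*

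**What the plan says.** **Allocation.** Protocol article, Randomisation and follow-up: "Treatment allocation will be determined by a computer-generated random number sequence that is stratified by study site and initial aortic diameter", with three diameter bands. The same section adds that "The Stanford study centre will utilize an independent randomization procedure implemented locally". Because that procedure runs within one centre, allocation there is also separate by site.

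**Centres.** Study organization: "Currently, there are nine study centres in total, seven in Australia, one in Leiden, Netherlands, and one in Stanford".

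**Primary model.** Statistical analysis gives an itemised list: "The fixed part of the model will contain the following covariates: Time for CTA measurements as a categorical", then ultrasound time as categorical, then "treatment, interaction between treatment and CTA time, and interaction between treatment and ultrasound time". Neither site nor diameter band appears. The baseline measurements are among the 11 repeated responses, and the difference between groups at baseline is set to zero. A later sentence allows further terms if needed. It follows the check of the covariance model, is conditional, and names neither factor.

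**Image reading.** Endpoints: "Central analysis of both CTA and ultrasound images will be performed at the study centre". Study organization says that Stanford "will utilise independent randomisation, medication concealment and imaging analysis", and places core imaging laboratories in both Townsville and Palo Alto.

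**The concern.** Stratified allocation balances the arms within each site, so differences in growth between sites contribute little to the true sampling variation of the treatment effect. A model without site does not know this. It counts between-site variation as residual noise, so its standard error exceeds the true one, its confidence interval is too wide and its test is conservative.

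The article lists the model terms one by one, and that list does not match its own randomisation scheme. This is therefore a stated choice, not a detail left to an unseen analysis plan.

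What is at stake is precision. The margin is thin: the article's own growth figures (mean 1.20, SD 1.16 mm/y, 30 % reduction) give a standardised effect of 0.31, below the 0.36 used to set the sample size.

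**Working it through.** **Inputs from the article** (Sample size and power calculations): mean growth 1.20 mm/y, SD 1.16, reduction 30 %, stated d = 0.36, 126 per group, power 80 %, α = 0.05, drop-out about 20 %, 300 recruited.

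**Assumed:** R², the share of growth variance that the site terms explain. The article gives no figure, so a range is shown. The test is taken as two-sided.

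**1. The plan's own figure.** A two-sided two-sample t-test with d = 0.36 and 80 % power needs 122.1, so 123 per group, within 3 % of the stated 126. Power at 126 is 81 %. The point about site does not alter that figure.

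**2. Effect size and number used here.**
- Difference = 0.30 × 1.20 = 0.36 mm/y
- d = 0.36 / 1.16 = 0.3103
- Completers per group = 300 × 0.80 / 2 = 120

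**3. Formulas** (normal approximation, arms balanced within site):
- SE ignoring site, in SD units: s = √(2/120) = 0.1291
- True SE, and SE with site in the model: s√(1 − R²)
- Overstatement of the SE: 1/√(1 − R²) − 1
- Power without site: Φ[(d/s − 1.96) / √(1 − R²)]
- Power with site: Φ[d / (s√(1 − R²)) − 1.96]
- Real type I error without site: 2 × [1 − Φ(1.96 / √(1 − R²))]

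Here d/s = 0.3103 / 0.1291 = 2.404. At R² = 0.10, √(1 − R²) = 0.9487. Power without site is Φ(0.444 / 0.9487) = Φ(0.468) = 68.0 %. Power with site is Φ(2.404 / 0.9487 − 1.96) = Φ(0.574) = 71.7 %.

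| R² due to site | SE overstated by | Power without site | Power with site | Gain (points) | Real type I error without site |
|---|---|---|---|---|---|
| 0 | 0 % | 67.2 % | 67.2 % | 0 | 0.050 |
| 0.02 | 1.0 % | 67.3 % | 68.0 % | 0.7 | 0.048 |
| 0.05 | 2.6 % | 67.6 % | 69.4 % | 1.8 | 0.044 |
| 0.10 | 5.4 % | 68.0 % | 71.7 % | 3.7 | 0.039 |

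Power without site also rises a little with R², because stratified allocation reduces the true sampling variation whichever model is fitted. Holding it at its R² = 0 value would overstate the gain.

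**4. Simulation to separate site from diameter.** Set-up: 252 patients, nine sites by three diameter bands, permuted blocks of 4, 24-month growth SD 2.32 mm (2 × 1.16) and effect 0.72 mm (2 × 0.36); 6,000 null and 3,000 power runs per scenario. Every model below conditions on baseline size, as an approximation to the planned mixed model.

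| Variance explained by site / baseline size | Quantity | Without site | With site | With site and bands |
|---|---|---|---|---|
| 0 / 0.10 | Type I error | 0.054 | 0.053 | 0.053 |
| 0.10 / 0.10 | Type I error | 0.038 | 0.047 | 0.046 |
| 0.10 / 0.10 | Power | 0.74 | 0.77 | 0.77 |
| 0.20 / 0.10 | Type I error | 0.028 | 0.053 | 0.051 |
| 0.20 / 0.10 | Power | 0.77 | 0.85 | 0.85 |

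Once baseline size is conditioned on, the diameter bands add nothing material. Site is what matters, and only to the extent that growth differs between sites.

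**The case against.** The strongest reply is that the planned analysis is valid as it stands. Omitting a balanced stratification factor costs only efficiency, and nothing in the article shows that growth differs by site. If R² is near zero, nothing is lost. That stands, and it limits the weight of the point.

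Four stronger readings are tempting, and the article supports none of them:

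- **That initial diameter is also left unadjusted.** It is absent from the covariate list, but the baseline measurements are responses with zero group difference specified. The model thus conditions on continuous baseline size, which is finer than three bands.
- **That an imbalance at Stanford goes uncorrected.** For aneurysm size it is handled in the same way. No other imbalance is identified, and no unequal allocation ratio is stated for Stanford. That the article describes no diameter bands there is silence in a condensed text.
- **That separate readers and local ultrasound machines bias the result.** A constant offset between readers or machines cancels in within-patient growth. Differences between sites in growth itself add variance; they could bias the estimate only if the allocation ratio also differed between sites.
- **That the type I error is inflated.** The direction is the opposite.

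It can also be said that adding terms for every factor at every time is not cheap, and that some of those terms cannot be estimated. Both are true, and the fix below is restricted accordingly.

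**Conclusion.** The mismatch is real: study site governs the allocation and is missing from an explicit list of model terms. The effect is a standard error that is too large by an amount that depends on an unstated figure. For site shares of 2 %, 5 % and 10 %, that is about 1.0 %, 2.6 % and 5.4 %, with about 0.7, 1.8 and 3.7 points of power to be recovered. These figures assume 120 completers per group, d = 0.31, a two-sided 5 % test, allocation balanced within site, and site terms that capture the assumed share. This is a worthwhile improvement in efficiency, not a flaw that invalidates the analysis.

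The conflict between Endpoints and Study organization over where images are analysed is separate. It needs correcting whatever is decided about the model, and is not itself evidence that site effects on growth exist.

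**What to change.** 1. Add study site to the fixed part of the model, with small Australian centres pooled and Leiden and Stanford kept separate. Define the pooling before unblinding.
2. Include the interaction of site with CTA time and with ultrasound time. Baseline is itself a response, so a site main effect alone would shift the level and would not adjust growth.
3. Leave out the site-by-12-month CTA terms for Leiden and Stanford, which do no CTA at that visit; these terms cannot be estimated.
4. State that initial diameter is accounted for through the baseline responses with zero group difference, and that diameter-band terms are therefore optional.
5. Reconcile the Endpoints statement on central image analysis with the two core laboratories and the independent imaging analysis at Stanford in Study organization.

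**Cost.** No new data, but more than a token number of parameters. If all Australian centres form one group, there are two site contrasts. Post-baseline they apply to eight measurements (two CTA volumes, two CTA diameters, four ultrasounds): 2 × 8 = 16, less 2 × 2 = 4 for the 12-month CTA terms, which leaves 12. Two contrasts at each of three baseline measurements add 6, for a total of 18. Each Australian group kept separate adds up to 8 + 3 = 11 more. Coarser pooling saves parameters but captures less of any variation between the Australian centres.
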